#### Recruitment

2.1.8

Pregnant women will be recruited through social media to complete a web-based survey. Inclusion criteria are the following: declaration of being pregnant, being able to complete the survey in the available languages (English, French, Spanish, Chinese, Polish, German, Russian, Italian, Ukrainian, Czech, Swedish, Albanian, Hebrew, Arabic, and Norwegian), answer the screening questions and provide informed consent for participation.

Exclusion criteria are the following: not providing online informed consent for participation or if the participant does not click on the submit button at the end of the survey, and women who do not answer all the GAD-7 and PHQ-9 scale questions.

#### Sample size

2.1.9

The estimated sample size is 500 for each country. This has been calculated using the CinCalc.com sample size calculator.^[25]^ Results of GAD-7 for the general population vary between 4,75 (+/−4.76) to 5,7 (+/− 4.9).^[20,26]^ For PHQ-9, the scores vary from 3,0 (+/−4,3; for population in age of 30–39) to 5,2 (+/− 5.06).^[26,27]^ To detect a 20% difference separately in anxiety (GAD-7 scale) and depression levels (PHQ-9 scale) between the studied countries using a power of 80% and a margin error of 0.05,^[25]^ the calculated sample size for GAD-7 is 394 in every single country and for PHQ-9 calculated sample size is 372 in every single country. Values yielding higher sample sizes will be used. This sample size will allow us to compare reported anxiety and depression levels among pregnant women in different countries around the world affected by the pandemic.

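### The PHQ-9 sample size rests on the less demanding of the plan's two inputs; at the other, 500 women per country give about 60% power for a 20% difference, not 80%

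*Protocol article*

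**What the plan says.** The Sample size section (2.1.9) of the protocol article sets the target first: "The estimated sample size is 500 for each country". It then quotes published scores as a range for each scale. For anxiety: "Results of GAD-7 for the general population vary between 4,75 (+/−4.76) to 5,7 (+/− 4.9"). For depression, "the scores vary from 3,0 (+/−4,3; for population in age of 30–39") up to a mean of 5.2 with SD 5.06.

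The aim of the calculation is "To detect a 20% difference separately in anxiety (GAD-7 scale) and depression levels (PHQ-9 scale) between the studied countries". The section fixes the power and the error level for this as follows: "using a power of 80% and a margin error of 0.05". The result is that "the calculated sample size for GAD-7 is 394 in every single country and for PHQ-9 calculated sample size is 372 in every single country". The next sentence reads "Values yielding higher sample sizes will be used".

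The section does not say which pair of inputs produced which figure. It gives no reason for setting either PHQ-9 pair aside.

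**The concern.** With two candidate inputs per scale and a stated preference for those giving the higher number, one expects the more demanding pair to be used for both scales. A 20% difference is relative to the mean, so a lower mean makes the target difference smaller in points. The SD does not fall in proportion: between the two PHQ-9 pairs the mean drops by 42% (5.2 to 3.0) and the SD by only 15% (5.06 to 4.3). The lower pair should therefore need many more women, yet the PHQ-9 figure is smaller than the GAD-7 one.

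The Introduction makes the comparison of anxiety and depression scores between countries the primary aim, and the Sample size section treats the two scales separately, so PHQ-9 needs adequate power in its own right. The Data collection section ends recruitment once the desired sample size is reached, so the number acts as the stopping target. If the power statement is wrong for PHQ-9, a null depression comparison between low-scoring countries could be taken as reliable evidence of no 20% difference when it is not.

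**Working it through.** **Inputs** (all from the Sample size section): power 80%; the 0.05 is taken as a two-sided significance level, since sidedness is not stated and two-sided reproduces both printed figures; target difference δ = 20% of the mean; equal groups. No allowance for dropout is stated. The Recruitment section excludes "women who do not answer all the GAD-7 and PHQ-9 scale questions", so 500 is taken as 500 analysable women.

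**Formula**, two independent means, normal approximation, per country:

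n = 2 × (1.960 + 0.842)² × SD² / δ² = 15.70 × (SD/δ)²

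**Reproducing the plan and running the unused pairs**

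| Scale | Mean (SD) | δ | (SD/δ)² | n | Plan states |
|---|---|---|---|---|---|
| GAD-7 | 4.75 (4.76) | 0.95 | 25.11 | 394.1 | 394 |
| GAD-7 | 5.7 (4.9) | 1.14 | 18.48 | 290.0 | – |
| PHQ-9 | 5.2 (5.06) | 1.04 | 23.67 | 371.6 | 372 |
| PHQ-9 | 3.0 (4.3) | 0.60 | 51.36 | 806.3 | – |

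Both printed figures are recovered, which identifies the method and the inputs. For GAD-7 the larger-n pair was used; for PHQ-9 the smaller-n pair. Rounded up, the unused PHQ-9 pair needs 807 per country (808 with the t distribution).

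**Power at the lower PHQ-9 pair**, with power = Φ(δ / (SD × √(2/n)) − 1.960), δ = 0.60, SD = 4.3:

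- n = 372: 0.60 / 0.3153 = 1.903, power 48%
- n = 394: 0.60 / 0.3064 = 1.958, power 50%
- n = 500: 0.60 / 0.2720 = 2.206, power 60%

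**Power at 500 for the other pairs**: PHQ-9 5.2, 90%; GAD-7 4.75, 88%; GAD-7 5.7, 96%.

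**Difference detectable with 80% power at 500**, 2.802 × SD × √(2/500):

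- SD 4.3: 0.76 points, or 25% of 3.0
- SD 5.06: 0.90 points, or 17% of 5.2

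**Could another convention rescue the claim?** One-sided 0.05 gives 71% power at n = 500 for the lower pair, still short of 80%, and yields 293 instead of 372 for the upper pair. Measuring the 20% from the other group's mean (δ = 3.0/0.8 − 3.0 = 0.75) gives 79%, but yields 238 instead of 372. Neither is the calculation the plan ran.

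**The case against.** Five points can be made for the plan.

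1. *The figure 372 is correct arithmetic.* True: it matches the 5.2 (5.06) pair. The fault lies in the choice of input and in the claim built on it.

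2. *The sentence on higher sample sizes may mean only that 394 governs over 372.* It follows directly after those two results, so this reading is open, and on it no rule is broken. But 394 gives 50% power at the lower PHQ-9 pair and 500 gives 60%, so the 80% claim fails there on either reading.

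3. *Pregnant women in a pandemic may well score above 3.0.* This is the strongest point. The 3.0 value belongs to a population aged 30–39, not to pregnant women; the Introduction describes pregnant women as especially prone to anxiety; and the Results section expects worried women to be more likely to respond. If the SD is interpolated linearly between the two pairs (an assumption), 500 per country reach 80% power from a mean of about 4.2 upward. Planning on 5.2 could be defended, but the plan does not defend it. It offers 3.0 to 5.2 as its range, the lower value comes from an age band that overlaps childbearing age, and the cited sources needed to choose between the pairs are not at hand.

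4. *The shortfall comes partly from using a relative difference.* Also true. In points, the study is more sensitive at SD 4.3 (0.76) than at 5.06 (0.90), and a 1.04-point difference at SD 4.3 has about 97% power with 500. But the plan states its target as 20%, and against that target the power is 60%.

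5. *The principal analysis is structural equation modelling, so this is only a planning approximation.* It is, but it is the calculation on which the plan bases its power claim. It also leaves out multiple comparisons between countries, any adjustment for which would lower power, and the planned reweighting, which generally does so too.

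**Conclusion.** The concern holds. The plan claims 80% power for a 20% difference on both scales without restriction. At its own lower PHQ-9 input, 500 per country give about 60%, and about 807 would be needed for 80%. At its upper input, 500 give about 90%. The GAD-7 claim is sound at both quoted values.

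This rests on a two-sided 0.05 level, equal groups, 500 analysable women per country, the SD paired with each mean, and no design effect or multiplicity adjustment. The shortfall applies only where PHQ-9 means lie towards the lower end of the quoted range; the documents do not settle whether they will. As it concerns a stated power for one of the two scores in the primary aim, it should be corrected.

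**What to change.** In the Sample size section:

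- State the input behind each PHQ-9 figure: 372 per country at mean 5.2, SD 5.06, and about 807 at mean 3.0, SD 4.3.
- Keep 500 per country and say what it delivers: 80% power for 0.76 PHQ-9 points at mean 3.0 (25% of the mean) or 0.90 points at mean 5.2 (17%), and 60% power for a 20% difference at mean 3.0.
- Replace the unqualified 80% claim for PHQ-9 with this statement.
- Make clear whether the sentence on higher sample sizes refers to the choice of inputs within a scale or only to taking 394 over 372.

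The cost is wording only. No extra participants are needed; the stated PHQ-9 power becomes less favourable.

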#### Data collection

2.1.10

The Pregmind International Research Group was formed, and a website was constructed for the international promotion of the study (www.pregmind.org).^[28]^ Data collection will begin with an initial social media post created on the the Pregmind Facebook fan page. The post will be prepared in the predefined languages and shared publicly. Campaigns will be set up to promote the study. Advertisements and posts will be shared on pages targeted towards pregnant women on every continent in the world in the predefined languages. We will also target closed pregnancy orientated groups via private messages on Facebook and invite them to post the study advertisement with the link to the survey on their pages.

The recruitment target will be reached when the desired sample size per region is achieved. We hope to collect data from at least one country from every continent. The survey will be translated into 15 languages, out of which 4 (English, Spanish, Chinese, Arabic) are widely spoken around the world and are not nationality related. For this study, the recruitment rate is difficult to predict. We expect data collection to take place at least six months for each language, based on similar previous studies of mental health.^[29]^ Recruitment rates may vary in different regions. Recruitment will not start simultaneously for all regions.

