Mothers have a strong desire to provide their children with a stable environment, however, the situation of the growing pandemic with strict limitations regarding social contacts and economic instability does not make a secure situation for procreation.^[5]^ Based on the current data, it seems that the severe acute respiratory syndrome coronavirus 2 (SARS-CoV-2) does not cause a severe course of infection in pregnant women as they are usually young and without co-morbidities.^[6]^ It is worth to underline that the COVID-19 pandemic is not only a public health crisis but also a social, demographic and economic one and it has a substantial negative psychosocial effect on everyone, including pregnant women. The resulting anxiety of pregnant women has a negative impact on pregnancy, such as increased risk of preeclampsia, depression, nausea, vomiting and could even cause preterm labor or miscarriage.^[1]^ What is more, maternal anxiety may lead to adverse effects of the newborns, like low birth weight, growth restriction or low APGAR score.^[13,14]^

The primary aim of our study is to compare differences in anxiety and depression scores of pregnant women between countries affected by the COVID-19 pandemic. The secondary aim is to assess demographic, economic, and social aspects affecting maternal anxiety and depression scores among pregnant women worldwide in the time of the COVID-19 pandemic. Finally, we will be able to compare differences in perception of the different aspects of the pandemic (social distancing, restrictions related to delivery) between countries and according to the epidemic status (number of infected patients, number of reported deaths). The comparisons will also be done according to the COVID-19 status of the participants.

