#### GAD-7 scale

2.1.5

Generalized Anxiety Disorder 7-item (GAD-7) questionnaire measures the severity of anxiety over the past two weeks. The GAD-7 questionnaire is a 7-question scale. There are four choices regarding the severity of symptoms: “not at all”, “several days”, “more than half the days” and “nearly every day”, which correspond to 0, 1, 2, and 3 points score, respectively (minimum total score 0, maximum 21).^[17]^ The summarized score is used to assess anxiety intensification. The scale is commonly used to diagnose generalized anxiety disorder in the general population. National Institute for Health and Care Excellence (NICE) recommends using this tool as a measurement of prenatal anxiety.^[18]^ The GAD-7 scale is the only scale besides the State-Trait Anxiety Inventory (STAI) that is validated for women in the prenatal period.^[4]^ The advantages of the GAD-7 scale are that it is more straightforward, easy to complete and that the interpretation is easier with fewer questions: 7 in GAD-7 vs. 20 in STAI. Moreover, the GAD-7 scale is available without cost and is easier to use on social media. In the general population a score of ≥ 10 allows diagnosis of generalized anxiety disorder.^[19]^ Nevertheless, in pregnant women, the cut-off point has been established as ≥7 with a sensitivity of 73.3% and specificity of 67.3%.^[20]^ (Table 1)

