#### Statistical analysis

2.1.11

Data will be kept anonymous and non-identifiable. For the statistical, analysis, R software^[30]^ and the Mplus computer program will be used.^[31]^ Data collection will include the most relevant demographic variables allowing us to compare collected data within a population. Reweighting and other techniques will allow adjustment for known or expected discrepancies between sample populations.^[32]^ To ensure comparability reweighting techniques, measurement invariance analysis will be performed. For the reweighting, we will use procedures suggested by Gelman and Carlin.^[32]^ We will collect external information about the distribution of age, place of residence, education level of pregnant women in the population, and adjust our sample to match the proportion in each country. If this is not possible because of the shortage of data, we will use propensity score matching^[33]^ and regression technique to balance the groups’ demographic distributions and make comparisons justifiable. Additionally, to ensure a valid comparison between countries, we will conduct a detailed measurement invariance analysis.^[34]^ Furthermore, we plan to perform regression analyses to explore potential associations between the reported anxiety, depression levels, and medical, sociodemographic, and pandemic related variables (including burdens related to social distancing). Altogether there will be 30 different variables. According to a rule of thumb “N > 104+m”, where N is the number of participants and m is the number of variables, the sample size will allow us to perform all planned analysis.^[35]^ Our main variables (GAD-7 and PHQ-9 scale) are measured by multiple indicators (questions), this opens the possibility to use Confirmatory Factor Analysis (CFA). This technique will allow us to assess the comparability of variables and, if necessary, address the problem of comparability using different latent variable modeling strategies.^[34]^ Principal analysis will be conducted using Structural Equation Modeling Framework which allows us to account not only for comparability problems but as well for measurement error.^[36]^

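### Regions are surveyed at different times and the variables named to make countries comparable are demographic only, so the primary country differences may be partly confounded with calendar time

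*Protocol article*

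**What the plan says.** The Introduction sets the comparison: "The primary aim of our study is to compare differences in anxiety and depression scores of pregnant women between countries affected by the COVID-19 pandemic". Under Results, the discussion of bias goes further and treats country differences as a consequence of the pandemic.

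The outcomes depend on when they are measured. GAD-7 "measures the severity of anxiety over the past two weeks" (2.1.5), and 2.1.6 gives PHQ-9 the same two-week window.

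On timing, 2.1.10 Data collection states:
- "Recruitment will not start simultaneously for all regions"
- "Recruitment rates may vary in different regions"
- "We expect data collection to take place at least six months for each language"
- "The recruitment target will be reached when the desired sample size per region is achieved"

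No common calendar window is given.

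On comparability, 2.1.11 Statistical analysis states "We will collect external information about the distribution of age, place of residence, education level of pregnant women in the population", and the sample is to be weighted to match. If population data are short, the fallback is propensity score matching and "regression technique to balance the groups’ demographic distributions and make comparisons justifiable". Measurement invariance analysis, confirmatory factor analysis and a structural equation model are added.

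Epidemic status (case and death counts) appears in the Introduction as a basis for comparing perceptions of the pandemic. Pandemic-related variables appear in 2.1.11 only in regressions that explore associations.

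**The concern.** A two-week symptom score taken during a moving epidemic reflects conditions at the time of response as well as the country of the respondent. By the protocol's own account, uncertainty and isolation raise anxiety and restrictions are spreading. If country A is surveyed mostly in one period and country B mostly in another, the raw contrast contains a country part and a timing part.

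Weighting on age, residence and education leaves the timing part in place. So does the measurement modelling, which addresses how the scales behave across countries, not when they were answered. The long bias discussion under Results does not mention timing.

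At stake is the reading of the primary result: a difference caused by the launch schedule could be reported as a difference between countries, or could hide one. A larger sample does not help, because it narrows the interval around a biased value.

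**Working it through.** **Inputs from 2.1.9 Sample size.** GAD-7 mean 4.75, SD 4.76. PHQ-9 mean 5.2, SD 5.06. Target difference 20% of the mean, so 0.2 × 4.75 = 0.95 and 0.2 × 5.2 = 1.04 points. Power 80%, error level 0.05 (taken as two-sided). Planned size 500 per country.

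**Reproducing the plan's figures.** n = 2 × [SD × (1.960 + 0.842) / difference]².
- GAD-7: 2 × (4.76 × 2.802 / 0.95)² = 394.1, against 394 stated.
- PHQ-9: 2 × (5.06 × 2.802 / 1.04)² = 371.6, against 372 stated.

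Both agree, so the same inputs are used below.

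**Precision at 500 per country.** SE = SD × √(2/500). GAD-7: 4.76 × 0.0632 = 0.301. PHQ-9: 5.06 × 0.0632 = 0.320. Power for the target differences is 88% (GAD-7) and 90% (PHQ-9).

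**Effect of a timing shift.** Suppose two countries do not differ, but timing moves one mean by b points. Then P(significant) = Φ(b/SE − 1.96) + Φ(−b/SE − 1.96). The protocol gives no value for b, so every value here is an assumption.

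| Assumed shift b (points) | GAD-7 | PHQ-9 |
|---|---|---|
| 0 | 5% | 5% |
| 0.25 | 13% | 12% |
| 0.5 | 38% | 35% |
| 0.75 | 70% | 65% |

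For example, GAD-7 at b = 0.5: 0.5/0.301 = 1.66, and Φ(1.66 − 1.96) = 0.38. That shift is about 0.1 SD (0.5/4.76) and about half the target difference.

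**The opposite error.** If a 0.5-point shift works against a true 0.95-point GAD-7 difference, the visible difference is 0.45. Power is then Φ(0.45/0.301 − 1.96) = 32% instead of 88%.

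**Does overlap remove the problem?** Assume two windows of equal length with even recruitment, starting 3 months apart, and a linear drift of 0.1 to 0.3 GAD-7 points per month. Average response dates differ by 3 months, so the bias is 0.3 to 0.9 points and the false-positive rate is 17% to 85%. Two six-month windows of this kind overlap by three months, so partial overlap alone does not protect the comparison.

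**The case against.** Several counter-arguments have weight.

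- **Confounding is not total.** A reader might infer that country and time cannot be separated at all, or that each country closes as soon as its target is met. The documents do not support this. Windows of at least six months may well overlap and average over several phases, and 2.1.10 says when the target counts as reached without giving a closing rule.
- **The adjustment set is not closed.** A reader might infer that only three variables will ever be used. They are the named reweighting variables. Section 2.1.11 also allows for other techniques and a demographic fallback, and does not list the covariates of the structural equation model. A fuller analysis plan may add some. What stands is that every variable named for balancing countries is demographic, and the staggered schedule is stated in the same article.
- **The size is hypothetical.** Setting the shift equal to the 0.95-point target gives 88%, but that merely returns the design's power and is no evidence of harm. The smaller shifts are also assumptions; they show sensitivity, not an expected bias.
- **Epidemic phase may be part of the effect of interest.** This is fair: the same month can be a different phase in different countries. It is a reason to state which comparison is meant. Launch date itself is not a property of a country.
- **A common all-country window would be costly.** If half the responses fell inside it (assumption), SE = 4.76 × √(2/250) = 0.43, and power for 0.95 points would fall from 88% to about 61%. This argues against making such a window primary.

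**Conclusion.** The concern holds in a limited form. The plan fixes staggered starts with no common window, measures outcomes that look back two weeks, and names only demographic variables to make countries comparable. Epidemic status is tied to a different comparison. Followed as written, the primary country differences may be partly confounded with the time of survey.

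The size cannot be determined from the protocol. The design is sensitive to small shifts: at 500 per country, an assumed 0.25 to 0.75 GAD-7 points would raise the false-positive rate from 5% to between 13% and 70%. These figures rest on the plan's SD, a two-sided 0.05 test of two means without weighting, and an assumed shift. They do not show that the country comparison is invalid.

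**What to change.** 1. Retain the submission date of every response. The protocol does not mention one; it is assumed to be available from the electronic survey system.
2. State in 2.1.11 whether countries are compared as observed, at the same date or at the same epidemic phase.
3. In the country-comparison model, include calendar month of response and the country's case and death counts for the two weeks before response. Report this beside the result without timing adjustment. If phase is held to be part of the country effect, the two results answer different questions and should be labelled so.
4. Add a sensitivity analysis restricted, for each pair of countries, to the calendar period in which both were open. Do not make a common window for all countries the primary analysis, given the possible loss of power.
5. Where two countries' windows do not overlap, adjustment for calendar time rests on extrapolation; the conclusion should then say that country and time cannot be separated.

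The cost is the work of linking dates to counts, slightly wider intervals, and some wording in 2.1.11. The questionnaire and sample size need not change.
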